#### **6.5 Maintaining and breaking the blind**

Part B is an observer-blind study. To maintain the quality of blinding, unblinded personnel belonging to the institution (person in charge of preparation for IP administration, person in charge of IP administration, pharmacist, CRA) will be designated. The unblinded personnel should perform only pre-defined tasks related to the study. In addition, a separate unblinded CRA will check the quantity and dispensing of the IP at the institution. The responsible unblinded CRA should perform only pre-defined tasks related to the study such as pharmacy monitoring and manufacturing and administration monitoring and should document the independent tasks. As a result, other investigators and sub-investigators, except for the unblinded personnel, will remain

blinded during the study period. The unblinded personnel in charge of preparation for IP administration and in charge of IP administration will prepare the IP in a place where the subject is not present and ask the subject to turn away at the time of IP administration so that the subject remains blinded during IP administration.

Allocation of unique codes by group will be managed by IWRS at the central enrollment center. In principle, randomization codes must remain blinded until the data lock for the analysis of the main study until the end of study and completion of analyses by the central laboratory so that assignment of each subject to relevant treatment group remains blinded. See Section 7.3.7 in this protocol for maintaining the blind during interim analysis.

If it is necessary to access a code during the study due to an SADR or the sponsor decides it is essential to access the code for the safety and right of the subject, the double blind may be broken, and blinding will be managed to ensure that only the unique code of the relevant subject is accessed.

Unblinding must be considered case by case and only in the event of a serious medical emergency in which knowledge of the study drug administered is necessary for appropriate treatment. In general, blind must be broken only if information on the treatment group may affect the subject's treatment. If the principal investigator or the sponsor considers that unblinding is necessary, the blind will be broken after contacting the sponsor or the principal investigator and obtaining their agreement. All unblinding must be clearly accounted for and documented. Subjects whose randomization codes are unblinded can no longer participate in the study.

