#### **8.5 Reporting suspected unexpected serious adverse reactions and actions to be taken**

If suspected unexpected serious adverse reactions (SUSAR) occur during the study period, the sponsor will report to the investigator, Minister of Food and Drug Safety, and if necessary, the IRB. For details, see Attachment 4. Good Clinical Practice and Guidance for Civil Petitioners 'Considerations for safety assessment and reporting by clinical trial sponsors', MFDS Rules on the Safety of Medicinal Products, etc.

- ③ UADRs that result in death or are life-threatening should be reported via telephone or fax

or in writing as soon as possible but no later than 7 days from when the event was reported or known to the sponsor. If all information according to ADR reporting is not reported, an additional detailed report should be submitted within 15 days from the relevant ADR was initially reported or known.

- ④ All other SUSARs will be reported within 15 days from when the event was reported or known to the sponsor.

In the event of “SUSARs” during the study, the principal investigator and the sub-investigator should make every effort to ensure the safety of subjects and take appropriate actions to minimize AEs in a timely manner. If there is additional information on the reported ADR, the sponsor should report until the relevant ADR is resolved (i.e., the ADR disappears or the subject is lost to follow-up).

If the study is conducted at multiple institutions, the sponsor should promptly notify to the institutions through the principal investigator.

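### Section 6.5 makes even emergency unblinding wait for another party's agreement, and its two paragraphs give conflicting grounds for opening a code

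*Protocol*

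**What the plan says.** All the operative text is in Protocol Section 6.5, in two neighbouring paragraphs.

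The earlier one opens two routes to a code. One is an adverse reaction: "If it is necessary to access a code during the study due to an SADR". The other is the sponsor's judgement: "the sponsor decides it is essential to access the code for the safety and right of the subject". Under either route, "blinding will be managed to ensure that only the unique code of the relevant subject is accessed".

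The later one is narrower. Each request is to be judged individually, with the ground limited as follows: "only in the event of a serious medical emergency in which knowledge of the study drug administered is necessary for appropriate treatment". A sentence qualified as a general rule adds that the blind should be broken only where the allocation could affect the subject's treatment. The procedure follows: "If the principal investigator or the sponsor considers that unblinding is necessary", then "the blind will be broken after contacting the sponsor or the principal investigator and obtaining their agreement". The paragraph ends by removing from the study any subject whose code has been opened.

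On who is blinded, the section says that "other investigators and sub-investigators, except for the unblinded personnel, will remain" blinded. The designated unblinded staff, who include the pharmacist, are restricted to pre-defined tasks, and releasing a code in an emergency is not among those named.

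Two other sections bear on the point. Section 8.5 sets the clock for fatal or life-threatening unexpected reactions at "no later than 7 days from when the event was reported or known to the sponsor", and 15 days for other unexpected serious reactions. Section 9.1 tolerates departures from the protocol where a subject faces immediate risk.

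**The concern.** An emergency code break exists for the case where a treating physician must know now what the subject received. A rule that makes it wait for a second party's consent puts that party's availability between the physician and the information. This is a first-in-human product (Section 1.2.3), so the route should work without improvisation.

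The second difficulty is that staff cannot tell which paragraph governs. A serious reaction whose treatment does not depend on the allocation may justify code access under the earlier paragraph and does not under the later one. Sponsor safety staff preparing an expedited report cannot tell whether they may look up the code themselves or must first ask the investigator, who is meant to stay blinded. Because opening a code ends participation, the choice between the paragraphs also decides whether a subject with a serious reaction remains under full follow-up or moves to the reduced follow-up for dropouts in Section 5.4.

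**Working it through.** No arithmetic applies: the protocol states no figure on this point and none follows from it. The check is to read the passages against each other.

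**Step 1. Is agreement a precondition or a notification?** The sentence puts the code break after both the contact and the agreement, so it is a precondition. The sentence starts from either the principal investigator or the sponsor and names the same two as the parties to be contacted. If the initiator could agree with itself the sentence would have no content, so the natural reading is reciprocal: the investigator needs the sponsor, and the sponsor needs the investigator.

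**Step 2. Is there a way round it in an emergency?**

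- Section 6.5 states no exception for urgency and no time limit.
- The codes are managed in the web response system, but no investigator access to it for emergencies is described.
- The pharmacist is unblinded and releases product through the system (Section 3.3), so the information exists at the site. The limit to pre-defined tasks gives that person no authority to release it.
- Section 9.1 excuses the deviation but provides no means of obtaining the code.

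**Step 3. Do the two paragraphs agree on the grounds?**

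| Situation | Earlier paragraph | Later paragraph |
|---|---|---|
| Emergency, treatment depends on the product | Covered if it is a serious adverse drug reaction or the sponsor judges access essential | Allowed, after agreement |
| Serious adverse drug reaction, treatment does not depend on the product | Allowed if access is necessary | Excluded by the emergency-only wording |
| Sponsor judges access essential for the subject, no emergency | Allowed on the sponsor's decision | Excluded by the same wording |
| Expedited report of an unexpected serious reaction | Can fall under the adverse-reaction ground | Excluded unless it is also a treatment emergency |

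The paragraphs can give the same answer in the first row. They conflict in the second and third, and in the fourth unless the reaction is also a treatment emergency.

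**Step 4. Does sponsor access need the investigator's agreement?** The later paragraph, read literally, says yes, because the sponsor is one of the two possible initiators. The earlier one lets the sponsor decide and mentions no consent. The agreement sentence can also be read as confined to unblinding for treatment. The text does not settle it.

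**Step 5. What does Section 8.5 add?** It sets deadlines and lists the investigator among the recipients of these reports. It describes no code access for reporting and does not say that the report carries the allocation.

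**The case against.** The best defence has four parts.

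- **The delay is hypothetical.** Section 9.1 covers immediate risk. Section 4.1.1.1 requires drugs, equipment and an investigator or designee during dosing and post-dose monitoring. Section 1.2.3 expects solicited events to be manageable with standard care. No passage describes a treatment that turns on the allocation. This limits the likely frequency and stands to that extent. It does not repair the rule, because Section 6.5 itself provides for such an emergency and then sets a condition on it.
- **The paragraphs can be harmonised.** The adverse-reaction ground is conditional on necessity, and the later paragraph could be defining necessity. That works for the first ground but not for the second, where the sponsor's view of the subject's safety and rights is broader than a treatment emergency.
- **Sponsor access may already be free of investigator consent.** This is a fair reading, so the point is put only as an ambiguity.
- **Operational detail belongs in a system manual.** A manual granting direct access would contradict the agreement condition that the protocol states.

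Three stronger readings are tempting and are not supported. A reader might infer that safety reporting unblinds the site. Asking for agreement, or withdrawing the subject, reveals that a code is being opened, not which product was given; access is limited to one subject, and Section 8.5 does not say that the allocation is passed on. A reader might try to quantify the wait from assumed sponsor office hours. The protocol states no staffing, and round-the-clock cover would make the wait negligible, so any such figure describes the assumption and not this trial. A reader might count every enrolled subject as affected. All are covered by the rule, but only a subject whose emergency treatment depends on the allocation is exposed to the delay.

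**Conclusion.** The concern holds in two parts. First, Section 6.5 makes emergency unblinding conditional on the other party's prior agreement, with no exception for urgency, so an investigator acting in the situation for which unblinding is meant could be delayed. This is a rule the protocol states, not a detail left for another document. Second, the two paragraphs of Section 6.5 contradict each other on the grounds for opening a code, and they leave open whether sponsor access needs the blinded investigator's agreement.

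The size cannot be expressed as a number. The event is probably rare, but the consequence falls on a subject's safety and the correction is cheap, so it should be made. The conclusion rests on reading the agreement sentence as reciprocal. It does not depend on any staffing assumption, and it does not extend to a claim that the observer blind or the safety comparison is compromised.

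**What to change.** Rewrite the two paragraphs of Section 6.5 as one rule on code access, with these elements:

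1. In an emergency where treatment depends on knowing the product, the investigator may open that one subject's code through the web response system without prior sponsor agreement, records the reason, and informs the sponsor afterwards.
2. One list of the grounds for opening a code replaces the two conflicting ones.
3. Any sponsor code access for expedited safety reporting is stated separately: it is done by staff outside the blinded team, without disclosing the arm to the site. The text says expressly whether the investigator's agreement has any role there.
4. The sentence ending participation for unblinded subjects is reconciled with item 3. If left unchanged, it would remove a subject because of sponsor-side access and so signal to the site that a code had been opened.

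The cost is the redrafted text in Section 6.5 and an emergency-access permission in the web response system. The downside is a possible extra code break that a prior discussion might have avoided; the record of reasons and the report to the sponsor keep it visible.

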- 11) If possible, subjects who are withdrawn from the study will visit the institution for required procedures. Those who are withdrawn prior to Visit 9 (end of main study visit) will perform Visit 9 procedures. Those who are withdrawn after Visit 9 will perform Visit 11 procedures (end of follow-up visit) except for blood sampling for immunogenicity testing. If consent is obtained from the subject, telephone visits will be conducted by a trained sub-investigator who will call the subject at the time points of Visit 10 (Week 26 after the 2nd dose of the IP) and Visit 11 (Week 52 after the 2nd dose of the IP) for serious ADRs and AESIs. Subject who has not performed administration of 2nd dose investigational product will conduct Visit 10 and Visit 11 on the basis of scheduled date of 2nd dose administration.
- 12) Concomitant drugs administered for SAEs and AESIs will be collected.
- 13) Status of SAEs and AESIs will be checked. In the event of an AESI, additional tests may be conducted as necessary at the discretion of the investigator, and if necessary, the DSMB may meet to review the case for status of ADR and enhanced disease.

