### **5.4 Criteria for subject discontinuation and withdrawal**

Those who are randomized but cannot participate in the study for the entire period for any reason will be classified as dropouts. Subjects may choose to discontinue the study at any time for any reason by requesting withdrawal. Or subjects may also be discontinued at any time for safety, behavioral, or administrative reasons at the discretion of the investigator or the sponsor. The investigator should ask about reasons for withdrawal and ask the subject to return for the last visit. If applicable, the investigator should make every effort to follow up on unresolved AEs.

For the following reasons, subjects may ask for withdrawal or may be discontinued or withdrawn

upon discussion with the investigator and the sponsor. In this case, the reasons and actions taken for the discontinuation and withdrawal should be recorded on the relevant document as well as on the CRF:

- ① The subject or his/her representative withdraws informed consent.
- ② Violation of the inclusion/exclusion criteria is identified during the course of the study.
- ③ The subject corresponds to exclusion criteria for 2nd dose.
- ④ The subject or his/her representative wants to discontinue the study due to unsatisfactory therapeutic effects during the study period.
- ⑤ The subject does not comply with instructions of the principal investigator or the sub-investigator.
- ⑥ Lost to follow-up.
- ⑦ The subject becomes pregnant during the study period.
- ⑧ Study participation is inappropriate for other reasons based on the judgment of the sponsor or the investigator

If possible, subjects who are withdrawn after Visit 2 and before Visit 9 (end of main study visit) will return to the institution for Visit 9 procedures. If possible, those who are withdrawn after Visit 9 will return to the institution for Visit 11 (end of follow-up visit) procedures except for blood sampling for immunogenicity testing. For safety follow-ups for dropouts, if consent is obtained from the subject, telephone visits will be conducted by a trained sub-investigator who will call the subject at the time points of Visit 10 (Week 26 after the 2nd dose of the IP) and Visit 11 (Week 52 after the 2nd dose of the IP) for SADRs and AESIs.

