## 7.2 Endpoints

### 7.2.1 Safety endpoints

- AEs
  - ① Immediate AEs occurring within 30 minutes after each IP dosing
  - ② Solicited local and systemic AEs occurring for 7 days (Day 0~ Day 6) after each IP dosing
    - ✓ Local AEs : pain, tenderness, erythema/redness, induration/swelling, itchiness
    - ✓ Systemic AEs : fever, fatigue/malaise, chills/rigors, headache, myalgia, joint pain, diarrhea, vomiting, abdominal pain, mucocutaneous reaction/rash, cough, acute bronchospasm, respiratory distress
  - ③ Unsolicited AEs occurring within 28 days after the last IP dosing
  - ④ SAEs occurring within 52 weeks after the last IP dosing
  - ⑤ AESIs occurring within 52 weeks after the last IP dosing
- Clinical laboratory tests (hematology/blood chemistry, urinalysis)
- Vital signs
- Physical examination

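### Breaking a subject's code ends study participation, and the dropout follow-up that replaces it is consent-dependent and, at least before Visit 9, narrower than the 52-week SAE endpoint

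*Protocol*

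**What the plan says.** **Trigger.** Section 6.5 contemplates a code break "If it is necessary to access a code during the study due to an SADR", or where the sponsor finds it essential for the subject's safety and rights. It then limits unblinding to individual decisions, "only in the event of a serious medical emergency in which knowledge of the study drug administered is necessary for appropriate treatment".

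**Consequence.** The same section ends: "Subjects whose randomization codes are unblinded can no longer participate in the study". It makes no exception and does not distinguish stopping treatment from stopping follow-up.

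**Status.** Under Section 5.4, randomized subjects who "cannot participate in the study for the entire period for any reason will be classified as dropouts".

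**Follow-up of dropouts.** Section 5.4 asks for one exit visit if possible (Visit 9 procedures before Visit 9, Visit 11 procedures without immunogenicity blood afterwards). Then: "For safety follow-ups for dropouts, if consent is obtained from the subject, telephone visits will be conducted by a trained sub-investigator". The calls fall at the Visit 10 and Visit 11 time points, and their scope in 5.4 is "dose of the IP) for SADRs and AESIs". Footnote 11 of the Schedule of Assessments has "dose of the IP) for serious ADRs and AESIs", and Section 4.2.9 agrees. Section 4.2.11, for withdrawals after Visit 9, says instead that calls may be made for SAEs and AESIs.

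**Endpoint.** Section 7.2.1 lists "SAEs occurring within 52 weeks after the last IP dosing". Section 8.2 collects SAEs and AESIs from the first dose to Visit 11, and Section 8.4 requires all SAEs over that period to be reported whatever their relationship to the product.

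**The concern.** A physician's learning the arm is a reason to mark later subjective reports as unblinded. It is not a reason to stop collecting data. Under this plan a break turns the subject into a dropout, and the follow-up that remains depends on consent and, for earlier withdrawals, on a causality judgement that the endpoint does not use. After a break, the person judging relatedness may know the arm.

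Removal is triggered by a medical emergency, so the missing follow-up cannot be assumed unrelated to safety. Safety and tolerability are the primary objective of Part A, the trial is first-in-human, and Section 7.3.6 imputes nothing. Because safety is analysed in all dosed subjects, an SAE that nobody asks about counts as no SAE, so the error is downward. Titres are laboratory measurements and stay valid after a break, yet the remaining samples are not taken.

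**Working it through.** The protocol gives no figure to reproduce here. The check sets the sections side by side and then bounds the size.

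**1. Call scope against endpoint**

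| Withdrawal | Provision | Events asked about |
|---|---|---|
| Before Visit 9 | 5.4, footnote 11, 4.2.9 | SADRs and AESIs |
| After Visit 9 | 5.4, footnote 11 | SADRs and AESIs |
| After Visit 9 | 4.2.11 | SAEs and AESIs (calls may be made) |
| Required for all | 7.2.1, 8.2, 8.4 | All SAEs and AESIs to Week 52 / Visit 11 |

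Before Visit 9, a period that contains both doses, every provision on call scope gives the narrow list. After Visit 9 the protocol disagrees with itself. The event type clearly at risk is a later SAE judged unrelated that is not an AESI. If the subject declines calls, no planned contact remains after the exit visit.

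**2. Immunogenicity samples not drawn**

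Scheduled samples are at Visits 2, 5, 8, 10 and 11. Visit 9 procedures (4.2.9) include none, and withdrawals after Visit 9 are expressly denied one.

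- Break after dose 1 and before Visit 5: Visits 5, 8, 10 and 11 lost (4). No post-dose result exists, so the subject also fails the FAS definition in 7.3.1.
- Break between Visits 5 and 8: Visits 8, 10 and 11 lost (3).
- Break between Visits 8 and 10: Visits 10 and 11 lost (2).
- Break between Visits 10 and 11: Visit 11 lost (1).

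The PPS, primary for immunogenicity, requires completion to Visit 9 under the protocol, so a break before then would ordinarily remove the subject from it.

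**3. Size (illustration only)**

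The documents give neither an unblinding rate nor an SAE rate. Assume k unblinded vaccine recipients, each with probability p of a later SAE that is outside the SADR/AESI scope and not otherwise reported. Planned vaccine recipients: 15 + 15 + 100 + 100 = 230, of 50 + 230 = 280 subjects. Expected subjects missed = k × p; understatement of incidence = 100 × k × p / 230 percentage points.

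| k | p | Expected missed | Understatement (points) |
|---|---|---|---|
| 1 | 1% | 0.01 | 0.00 |
| 5 | 5% | 0.25 | 0.11 |
| 5 | 20% | 1.0 | 0.43 |
| 10 | 50% | 5.0 | 2.17 |

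Pooling hides the small groups. One missed case in a Part A vaccine group is 1/15 = 6.7 percentage points; in a Part B dose group it is 1/100 = 1.0 point.

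**The case against.** The best defence is that little is lost. An SADR does not unblind automatically; 6.5 demands a serious emergency in which treatment knowledge is needed. The event behind the break is already recorded, and 5.4 and 8.2 require it to be followed. An exit visit is requested. For a subject who consents, the calls fall at the same two time points as the scheduled contacts after Visit 9. Section 4.2.11 gives the full SAE scope for late withdrawals, and 8.4 requires every SAE to be reported. The FAS keeps titres already obtained once there is one post-dose result. The safety analysis is descriptive and the study tests no hypothesis.

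All of this stands, and it limits the size. It does not remove the gap. Section 8.4 governs events that become known, while the planned contact with early withdrawals does not ask for all SAEs. Section 4.2.11 conflicts with 5.4 and footnote 11. Nothing keeps an unblinded subject in scheduled follow-up.

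It is also fair that the call-scope mismatch affects every dropout, not only unblinded subjects. Section 5.3, for example, sends a subject with a product-related SAE after dose 1 to 5.4 without any code break. A change to 6.5 alone would leave that untouched.

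**Conclusion.** The concern holds in limited form. As written, a code break stops scheduled follow-up and replaces it with consent-dependent calls that are narrower than the SAE endpoint before Visit 9 and inconsistently defined after it. It also forfeits one to four immunogenicity samples. The number affected is likely small: the illustration runs from a negligible effect to about 2 points of pooled SAE incidence under heavy assumptions. The reason to act is that the loss follows a medical emergency, and so may be informative, and is avoidable at little cost.

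A reader might infer more, without support:

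- That subjects with serious reactions generally leave, that the unblinded include most SADR cases, or that they are mainly vaccinees. Breaks are discretionary and the documents give no rates by event or arm.
- That each such subject loses 52 weeks of SAE data. The triggering event is followed, and consenting subjects are called at both later time points.
- That the exclusion of placebo subjects from DSMB review (7.3.8) makes code breaks common. That section does not say DSMB review breaks individual codes under 6.5.

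**What to change.** 1. **Section 6.5.** Replace the sentence ending participation with one that separates unblinding from follow-up. A subject whose code is broken is flagged as unblinded from that date and, if willing, stays in scheduled follow-up for all SAEs and AESIs to Visit 11 and for the remaining scheduled serology, including Visit 8 if it is still due. AEs recorded after the break are marked as unblinded. A code break alone should not make the subject a dropout under 5.4. Whether any further dose is given is a separate clinical matter, not addressed here.
2. **Footnote 11, 4.2.9, 4.2.11 and 5.4.** Reconcile the call scope for dropouts across these places and with the all-SAE endpoint in 7.2.1 and the rules in 8.2 and 8.4. This also covers subjects who drop out for other reasons.

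The cost is a text amendment in five places, with the approval that Section 9.2 requires, and a dated unblinding flag in the CRF. The downside is that causality judgements and subjective AE reports after the break are made with the arm possibly known. They must be flagged so that they can be shown separately. Titres need no such caution.
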